## Abstract

**Background:**

The standard technique for the placement of ventricular catheters (VC) comprises a high proportion of malpositioning of the catheter (12.5 to 40%). Technical advances such as neuronavigation or ultrasound have been shown to increase the accuracy of the procedure. Since these means result in significant technical and time consuming efforts, they are used for selected cases only. In order to simplify the controlled placement of ventricular catheters a newly developed smartphone assisted guiding tool has been introduced. In this study the efficacy and safety of this guiding tool is determined.

**Methods/design:**

This study is a multicentre, randomised, controlled trial. A total of 144 patients planned for an elective shunting procedure will be enrolled throughout 10 study centres within two years. The primary objective of the trial is to show the superiority of the guided placement in comparison to the standard freehand technique of ventricular catheter application. Patients will be followed up for 30 days after the operation in regard to image-based evaluation of the catheter position as well as possible shunt dysfunction and complications.

**Discussion:**

The Guided Application of Ventricular Catheters (GAVCA) trial compares the guided catheter positioning with the standard freehand technique of catheter placement in hydrocephalic patients. If superiority is shown, the standard technique may be changed with the advantage of a more reliable and safer positioning of the ventricular catheter with just a slight effort in time and pre-operative planning.

**Trial registration:**

The GAVCA trial is registered at ClinicalTrials.gov under the number NCT01811589.

## Background

The transcortical puncture of the ventricles is considered to be a simple neurosurgical procedure and is performed as one of the first procedures in neurosurgical training [1]. The ventricular catheter is considered as a lifelong functioning implant in the case of a shunting procedure; therefore special focus should be dedicated to the accurate positioning of the catheter as a correlation between catheter position and risk for proximal shunt obstruction is already described [2-7]. Several studies estimate the proportion of inaccuracy in the standard freehand technique to be in the range of 12.5 to 40% [2,4,8,9]. This freehand technique is based on the guidance by anatomical landmarks and the experience of the surgeon. In selected, more complicated cases technical advances such as neuronavigation or ultrasound might be used. However, this comprises high technical and time consuming efforts within a rather short procedure [4,10-13]. Seeing this problem, a more simplified technique is needed to be applied in a wide range of procedures. A mechanical catheter-guiding instrument was developed which enables a controlled placement of the catheters by applying one individual measure to the patients’ anatomy [14]. The instrument is suitable for a frontal pre-coronal approach. In earlier measurements based on MR images by using the foramen of Monro as a target, the angle towards the tangent of the skull surface was found to be relevant for the correct trajectory of puncture. Hereby, it could be shown that this angle is always rectangular in the sagittal plane whereas in the coronal plane an individual angulation must be measured respectively, with a mean deviation from rectangular of 1.96° ± 2.75° towards the medial margin up to 9.56° ± 4.14° towards the lateral margin of the ventricle [14]. That led to the development of the ventricular catheter guide which addresses a strict trajectory of a 90° angle to the sagittal surface of the skull and may be adjusted to an individual angle to the coronal surface. The measurements for the correct adjustment of the catheter guide are done on a coronal section of the cranium at a frontal paramedian entry point. Since regular DICOM viewing software does not allow an easy measurement of this parameter, this is facilitated in an iPhone application software (Version 1.1.1 for iOS6.1, Apple Inc., Cupertino, USA). Herein, the guiding instrument can virtually be visualised and placed on the skull of a coronal reconstructed section of the cranium for easy measurement of the trajectory’s angle towards the coronal surface of the skull.

The technical feasibility of the smartphone assisted guiding tool was verified in a single centre retrospective study [14]. In comparison to earlier studies on freehand ventricular placement, an advantage in the first pass cannulation and positioning was achieved.

The aim of the Guided Application of Ventricular Catheters (GAVCA) study is to show that the ventricular catheter guiding tool is superior to the standard freehand technique in terms of correct catheter position within the ipsilateral ventricle in a randomised multicentre trial.

## Methods/design

### Objectives

This study is designed as a prospective, randomized, two-armed, multicentre trial comparing two surgical procedures (Figure 1). The primary objective of the study is to prove the superiority of the guided ventricular catheter placement (treatment arm 1) versus standard freehand technique (treatment arm 2) in terms of correct catheter position in the ipsilateral ventricle.

**Figure 1 F1:**
[figure not shown]
Study protocol flow chart representing the randomisation process.

#### Primary endpoints

– the proportion of primary grade I or grade Ib catheter tip position in the ipsilateral ventricle

#### Secondary endpoints

– number of cannulation attempts until cerebrospinal fluid flow sets in

– the proportion of correct intraventricular localisation of the perforated catheter part

– early shunt failures

– complication rates (adverse events)

### Interventions

The procedure of cerebrospinal fluid shunting in hydrocephalus patients is an accepted neurosurgical standard. The placement of a ventricular catheter is a surgical skill that is taught early within neurosurgical training. Therefore, every neurosurgeon and neurosurgical resident is applicable to undertake the procedure within the trial as long as the handling of the catheter guide was taught within a standardised training.

The surgical technique is standardised as follows. The preparation of the skin flap is performed in order to expose at least 2 cm in diameter of the precoronal paramedian skull surface. One bore hole trepanation is performed at a localisation of 10 to 12.5 cm measured from nasion and 2 to 3.5 cm measured from midline in accordance to the individualised software measurements. The dura mater is to be coagulated and opened in order to enable the catheter puncture without being deviated at the dura level. The brain surface is punctiformly coagulated to open the leptomeningeal layers.

In treatment arm 1, the catheter guide is used with the individual parameters of coronal angulation to the skull surface and catheter length measured in a coronal section of the cranium with the catheter guide application software.

In treatment arm 2, the catheter placement is undertaken in freehand technique.

In both arms, the catheter is fixed by a rectangular redirector of the catheter from the bore hole to the subcutaneous tissue, such as a bore hole reservoir or a 90° connector.

In case of an unsuccessful cannulation, the surgeon will re-try the puncture in the freehand group. In the guided catheter group, the surgeon will repeat the use of the guide in case any mistakes in its application are detected and may need to be corrected, otherwise a crossover to the freehand technique will be performed.

### Follow-up

At the day of surgery relevant perioperative parameters are reported. This includes, for both treatment arms, the age, sex, the underlying cause for hydrocephalus, the ventricular width according to the frontal occipital horn ratio (FOHR) and the frontal occipital width ratio (FOHWR), the personal and the device-specific expertise level of the operating surgeon, the number of cannulation attempts, the type of ventricular catheter, the localisation of the entry point, the time of surgery, and any adverse events.

The individual angulation of the catheter guide and the length of the implanted catheter are reported for the treatment arm as measured in the ventricular guide application software. After surgery a MRI-scan or CT-scan as postoperative control is performed to document the catheter position and any adverse events, such as intra-cerebral haemorrhage. The follow-up examinations will be performed on the day of discharge from hospital and 30 to 40 days after surgery in order to report catheter dysfunction with the need of a re-operation and serious adverse events (Table 1).

**Table 1 T1:** Study protocol representing the relevant CRF visits

**Method**	**Visit 0**	**Visit 1 pre-OP**	**Visit 2 peri-OP**	**Visit 3 discharge**	**Visit 4 end of study**	**CT catheter-control**
**screening, consent, inclusion**	x					
**randomisation, patient data**		x				
**surgery**			x			
**perioperative study visit, complications**			x			
**study visit, complications, early shunt failure**				x	x	
**postoperative brain scan (until study visit 4)**						x

### Rating of the catheter position

The catheter position is rated in a centralised manner in regard to the 2 cm tip of the catheter (perforated part) by a neuroradiologist. The neuroradiologist is blinded for the treatment arm and outcome of the patient and evaluates the position of the catheter on the postoperative reconstructed MRI or CT scans, which were performed within 30 days after surgery (Figure 2). The rating will be performed using the following protocol [15].

– **grade I**: ideal catheter position without contact to the ventricular wall of more than 0.5 cm

– **grade Ib**: contact to the medial and lateral ventricular wall in the case the ventricular width equals the catheter diameter

– **grade II**: contact to the ventricular wall or the choroid plexus of more than 0.5 cm

– **grade III**: partly intraventricular position of the catheter (less than 1.5 cm intraventricular)

– **grade IV**: extraventricular position of the catheter (less than 0.5 cm intraventricular)

**Figure 2 F2:**
[figure not shown]
**Catheter position rating scale. Grade I**: ideal catheter position with contact to the ventricular wall less than 0.5 cm. **Grade Ib**: contact to the medial and lateral ventricular wall in the case of ventricular width equals the catheter diameter. **Grade II**: contact to the ventricular wall or the choroid plexus of more than 0.5 cm. **Grade III**: only partial intraventricular position of the catheter (less than 1.5 cm intraventricular). **Grade IV**: extraventricular position of the catheter (less than 0.5 cm intraventricular).

In addition, the postoperative image will be evaluated for the position of the respective catheter tip in the ipsilateral, contralateral, third ventricle or in any extraventricular compartment. Therefore the length of the intraventricular catheter part will be measured. Compared to preoperative ventricular width values, the postoperative FOHR and FOHWR will also be measured. As adverse events in imaging, any possible bleeding or air inclusions will be detected.

### Study tool

The catheter guide is a medical instrument, which is approved and bears the CE-Mark (Thomale Guide, certificate registration number: 009066 MR2) It is produced by the Miethke company (Potsdam, Germany) and distributed by Aesculap, Inc. (Tuttlingen, Germany). The catheter guide allows an individual angulation in the coronal plane whereas the angulation in the sagittal plane is in a strict rectangular direction (Figure 3).

**Figure 3 F3:**
[figure not shown]
**Ventricular catheter guide placed on the surface of the skull model as used during surgery. A**: In the coronal plane, the individual angulation towards the skull surface can be adjusted. **B**: In the sagittal plane, the angulation to the skull surface is fixed at 90°.

### Study software

In order to identify the ideal trajectory in the coronal plane an image processing software (https://itunes.apple.com/en/app/thomale-guide-application/id648839804?mt=8 Thomale Guide App, Version 1.1.1 for iOS 6.1, Apple Inc., Cupertino, USA) was developed for the iPhone/iPad, which is also approved in the EU (certificate registration number: 009066 MR2). This software can be downloaded for free from the Apple app store [14]. The application is used to measure the angle of the trajectory, the catheter length and the position of the bore hole relative to midline from imported images (Figure 4). Alternatively, the individual patient’s parameters can also be obtained by processing on an adequate DICOM-viewer-software (Centricity, Gentricity 3.0, General Electrics Inc., Fairfield, USA), if the user is familiar with that.

**Figure 4 F4:**
[figure not shown]
**Measurements acquired through the smartphone application. A**: Coronal MRI section with moderate enlarged ventricles with virtual placement of the guide on the skull surface. Angulation of catheter trajectory (red dotted line) is measured at 10° deviation from 90° (light blue dotted line) tilting the guiding tube towards the midline. The catheter length (green dotted line) is measured at 67 mm. **B**: Coronal CT reconstruction along body axis with the measurements revealing an angulation of 5.2° deviation from rectangular with the guiding tube tilt towards the midline and a catheter length of 69 mm.

### Trial population

The trial population will be recruited consecutively from the hydrocephalic patients who are scheduled for a shunting procedure in the participating medical centres. The participation in the trial ends with the final visit at Day 30 after surgery. Further follow-up visits are not scheduled. A detailed overview of the eligibility criteria are given as follows.

#### Inclusion criteria

– hydrocephalic patient needing a shunting procedure

– fronto-occipital horn ratio (FOHR) <0.5 [16]

– positioning via a mature brain tissue trajectory

– pre-coronal/frontal approach to the ventricle

– signed informed consent

#### Exclusion criteria

– previous known uneven bone surface at the site of the approach

– slit ventricles with an fronto-occipital horn width ratio (FOHWR) <0.05 [17]

– participation in other clinical trials with interfering endpoints

– patients unable to give informed consent

### Sample size

The sample size was determined to verify the hypothesis of superiority of treatment arm 1 (guided catheter placement) in comparison to treatment arm 2 (freehand technique) in regard to the proportion of primary cannulation of grade I or grade Ib in the ipsilateral ventricle. A successful catheter positioning of grade I or Ib in the ipsilateral ventricle is regarded as a positive response.

As we calculate with a 5% non-responder rate in treatment arm 1, the positive response in treatment arm 1 was reduced to 78.8% according to the weighted average. The difference between the two balanced patient cohorts is rated on a one-sided Chi-squared test with a significance of 2.5% and a power of 80%. Sixty-five patients are to be enrolled in each treatment arm as calculated with the software STATA 12.1, (StataCorp, College Station, TX, USA). Including a 10% dropout rate, the number increases to 72 patients per treatment arm.

### Randomisation and blinding

Patients’ allocation to both study arms is balanced (1:1). In order to minimise the size differences between groups, blocks of random length are used. The randomisation system is integrated into a web-based, password protected electronic case report form (http://www.studiesportal.com, Aesculap, Inc., Tuttlingen, Germany). Blinding of the operating surgeon is not feasible. The response (catheter position) is rated on the postoperative scans by the treatment-blinded outcome evaluator, which is an experienced neuroradiologist.

### Statistical analysis

#### Primary variable

The proportion of patients with a primary placement of grade I or Ib position of the catheter in the ipsilateral ventricle, as well as associated 95% confidence intervals, will be reported for each treatment arm. The study null hypothesis, which is to reject, states that the catheter guided treatment arm is equal or inferior to the freehand technique arm regarding the proportion of correct catheter positioning in the ipsilateral ventricle. This null hypothesis has to be disproved to state the superiority of the catheter guide treatment.

*H 0*: *P*_
*TG*
_ – *P*_FH_ < = 0 (*P*_
*TG*
_ < =*P*_
*FH*
_);

*H 1*: *P*_TG_ – *P*_
*FH*
_ > 0 (*P*_
*TG*
_ > *P*_
*FH*
_).

*P* is equal to the responder rate (TG – Thomale Guide, FH – freehand)

The analysis will be based on the intention-to-treat population in order to include catheter guide treatment problems with a change in the intraoperative treatment of the patient (cross-over). In the case of non-applicability of the catheter guide (for example, uneven bony surface) in patients randomised into the catheter guide treatment arm, they will be treated according to the freehand technique treatment arm. This is also applicable for patients with unsuccessful cannulation of the ventricle in the catheter guide treatment arm according to the decision of the operating surgeon. In the intention-to-treat analysis, all these cross-over patients will be analysed in the catheter guide treatment arm.

In a secondary step, a per-protocol reporting will be done, which excludes cross-over patients.

In a tertiary analysis as-treated reporting (safety evaluation) is foreseen.

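### The per-protocol set removes cross-over patients, who arise only in the guided arm and include failed guided cannulations, so its results are expected to favour the guide; the confirmatory intention-to-treat analysis is not affected

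*Protocol article*

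**What the plan says.** The section Primary variable makes intention-to-treat the main analysis and gives the reason: "The analysis will be based on the intention-to-treat population in order to include catheter guide treatment problems". Under it, "all these cross-over patients will be analysed in the catheter guide treatment arm".

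The same section gives two routes to cross-over, both starting in the guided arm. The first is that the guide cannot be applied, for example on uneven bone: "in patients randomised into the catheter guide treatment arm, they will be treated according to the freehand technique treatment arm". The second is a failed guided pass: "This is also applicable for patients with unsuccessful cannulation of the ventricle in the catheter guide treatment arm", at the operating surgeon's decision.

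The section Interventions describes a failed pass in each arm. For freehand: "In case of an unsuccessful cannulation, the surgeon will re-try the puncture in the freehand group". For the guide, the device is used again if a mistake in its application is found; "otherwise a crossover to the freehand technique will be performed".

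The per-protocol set is then fixed by one rule: "In a secondary step, a per-protocol reporting will be done, which excludes cross-over patients." The section Secondary variables uses this set, alongside intention-to-treat, for the number of attempts, the position of the perforated part and complications. Early shunt failure is reported as treated.

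**The concern.** The rule excludes patients on an event that happens after randomisation, is closely tied to the endpoint, can occur in one arm only, and depends partly on a surgeon who is not blinded. A patient who crosses over after a failed guided pass has also followed the protocol, because the Interventions section prescribes that step.

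What is at stake is how the per-protocol results are read. They are the first results named after the primary analysis. A per-protocol difference larger than the intention-to-treat difference would normally be taken as corroboration, yet here selection alone could produce it.

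**Working it through.** **Step 1: the same event in each arm.**

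| Event | Guided arm | Freehand arm |
|---|---|---|
| Technique cannot be applied | Treated freehand; cross-over; excluded | No such route described |
| Failed pass, application mistake found | Guide used again; kept | Not applicable |
| Failed pass, otherwise | Cross-over; excluded | Re-tried; kept |
| Final grade II to IV without cross-over | Kept | Kept |

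The rule can remove no freehand patient. It removes some guided failures, though not all of them.

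**Step 2: number of attempts.** No assumed rate is needed for the direction. A patient who crosses over after a failed guided pass has at least one guided and one freehand attempt, so at least two. That patient is removed. A freehand patient with two or more attempts stays.

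**Step 3: inputs for the primary variable.** The article gives 78.8% for the guided arm, a 5% non-responder rate, 65 patients per arm, one-sided 2.5% and 80% power. It gives neither a freehand success rate nor a cross-over rate, so 65 cannot be reproduced from stated inputs alone. An assumed freehand rate of 56% fits well. With 80% before dilution, 0.95 × 80% + 0.05 × 56% = 78.8%, and 78.8% against 56% needs 66 per arm (power at 65 is 79.9%). Below, 56% and 70% are assumed success rates and 5, 10 and 15% are assumed cross-over shares.

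**Step 4: formula.** Let p be the guided intention-to-treat rate, c the cross-over share and r the success rate among cross-overs. Then:

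- guided per-protocol rate = (p − c·r)/(1 − c)
- shift from intention-to-treat = c·(p − r)/(1 − c)

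The freehand rate does not change. The shift is zero when r = p and positive when r < p.

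**Step 5: results with no true difference (p in both arms).** For example, with p = 0.56, c = 0.10 and r = 0, the guided per-protocol rate is 0.56/0.90 = 62.2%, a shift of +6.2 points.

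| p | r | c = 5% | c = 10% | c = 15% |
|---|---|---|---|---|
| 56% | p | 0 | 0 | 0 |
| 56% | p/2 | +1.5 | +3.1 | +4.9 |
| 56% | 0 | +2.9 | +6.2 | +9.9 |
| 70% | p | 0 | 0 | 0 |
| 70% | p/2 | +1.8 | +3.9 | +6.2 |
| 70% | 0 | +3.7 | +7.8 | +12.4 |

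(percentage points)

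**Step 6: the design scenario.** Take 78.8% against an assumed 56%, and read the 5% as cross-overs, which is itself an inference. The intention-to-treat difference is 22.8 points. Per protocol it becomes 24.0 points if cross-overs succeed at 56%, 25.5 if at 28%, and 26.9 if none succeed.

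**Step 7: illustration only.** If a one-sided 2.5% test were run per protocol with 65 per arm and no true difference, simulation puts rejection at about 5 to 7%, 10 to 16% and 20 to 35% for c = 5, 10 and 15% with r = 0. With r = p/2 it is about 4%, 5 to 7% and 8 to 11%.

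**The case against.** Dropping patients who did not complete their allocated technique is a conventional per-protocol definition. Intention-to-treat was chosen here precisely to keep the guide's problems in view. The secondary variables are shown on both sets, so any gap will be visible. All of this stands, and it limits the weight of the point.

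The size is also uncertain. Patients in whom the guide could not be applied have had no failed pass and may well reach grade I or Ib; dropping them does no harm if they succeed like the rest. At 5% cross-over the two sets differ by about three of 65 patients. The r = 0 rows are therefore an upper bound.

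A reader might infer three stronger things that the article does not support:

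- **That the trial's false-positive rate is inflated.** The confirmatory test is on intention-to-treat. The per-protocol step is called reporting, with no test named for it, so the rates in step 7 are not error rates of the plan.
- **That 5% cross-over is planned.** The Sample size section speaks of a non-responder rate.
- **That the per-protocol rate is success among patients in whom the guide worked, and is bound to exceed the intention-to-treat rate.** Guided patients with grade II to IV and no cross-over remain, as do those re-punctured with the guide. The excess arises only if cross-overs succeed less often than other guided patients. That is likely, since a failed pass defines one route, but it is not certain.

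None of this removes the one-sidedness of the rule or its effect on the number of attempts.

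**Conclusion.** The concern holds as a moderate one. The stated rule excludes patients from one arm only, partly because the allocated technique failed, so the per-protocol results are expected to favour the guide. For the number of attempts this follows from the rule itself.

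For the primary variable, with no true difference and the assumed rates above, the gain is about 1.5 to 6 points if cross-overs succeed at half the arm's rate and 2.9 to 12.4 points in the worst case. It is zero if they succeed like other guided patients. The direction depends on how cross-overs fare relative to the rest of the guided arm, not on the freehand rate. The superiority test, its level and its power are unaffected.

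**What to change.** Redefine the per-protocol set in the Primary variable section:

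- Exclude only patients in whom the allocated technique was never attempted for a reason found before puncture, with the same rule in both arms. The freehand side may have little to act on, but stating it keeps the rule symmetric.
- Keep patients with an attempted but failed guided cannulation in the guided arm.
- Apply the definition of primary placement identically to first-pass failures in both arms. Scoring failed guided passes as failures while crediting re-tried freehand patients with their final grade would reverse the bias.
- Report cross-overs by reason, and label the per-protocol set as supportive only.

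This costs a few lines of text and changes nothing in surgery. Attempts are already recorded (Follow-up). The reason for each cross-over is also needed; the article does not list it among the perioperative items, although the case report form may hold it. The downside is that the per-protocol result may be slightly less favourable to the guide.
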